### Secondary measures

*Child Depression Inventory (CDI)*[46]*.* The CDI is one of the most widely utilized and cited diagnostic instruments for depression in children [47,48]. It is a 27-item self-report assessment, adapted from the Beck Depression Inventory [48]. Research has found the CDI test-retest reliability to be moderate range for clinical samples and adequate internal consistency, concurrent validity [47] and discriminant validity have been established [46].

*Children’s Anxiety Life Interference Scale - Child Form (CALIS-C)*[49]*- Adolescents only.* The CALIS-C is a 10-item self-report questionnaire about the impact of fears and worries on an adolescent’s quality of life, self-efficacy and well-being [49]. Reliability estimates were found to be adequate; moderate-to-strong convergent validity and discriminant validity have been observed [49]. The CALIS-C also demonstrates sensitivity to change [49].

*McMaster Family Assessment Device (FAD)*[50]*.* The FAD is a 53-item inventory completed by caregivers on the structure, organization and patterns of transactions within families [50]. Six dimensions of family functioning are identified in the model including Problem Solving, Communication, Roles, Affective Responsiveness, Affective Involvement and Behavioral Control [50]. Moderate-to-strong reliabilities have been obtained for the FAD [50]. It also has established discriminant [50] and concurrent validity [51].

### Process measures – Adolescents only

*Avoidance & Fusion Questionnaire - Youth (AFQ-Y)*[52]*.* The AFQ-Y is a 17-item self-report measure of cognitive fusion and experiential avoidance for children and adolescents [52]. Confirmatory factor analysis has supported the hypothesized one-factor model of the AFQ-Y and internal consistency reliability was also found to be strong [52].

*Child and Adolescent Mindfulness Measure (CAMM-20)*[53]*.* The CAMM-20 is a 20-item self-report questionnaire that focuses on internal and external awareness as well as mindfulness [53]. Exploratory factor analysis found support for a CAMM-20 two-factor model of ‘Observing’, noticing and attending to stimuli including internal and external phenomena, and ‘Acting with Awareness (AWA)’ including items that involve absolute focus and engagement with activity in the present moment [53]. The internal consistency of both scales was in the moderate range [53].

*Positive and Negative Affect Schedule (PANAS-X)*[54]*.* The PANAS-X is a 20-item measure of emotional experience across two scales, Positive Affect (PA) and Negative Affect (NA) [55]. Respondents rate the extent to which they have experienced an emotion over a prescribed time [55]. Internal consistency reliabilities were found to be in the moderate-to-high range across both scales, and low correlations between the NA and PA scales indicate good discriminant validity [54], with similar results obtained in a sample of adolescents [53]. The PANAS-X demonstrates adequate construct validity and high internal consistency [54].

*Toronto Alexithymia Scale (TAS-20)*[56]*.* The TAS-20 is a 20-item self-report inventory of the construct of alexithymia and produces scores in three related domains: difficulty identifying feelings, difficulty describing feelings and externally-orientated thinking [57]. The TAS-20 has been found to demonstrate adequate convergent, discriminant and concurrent validity [58].

*Valued Living Questionnaire (VLQ)*[59]*.* The VLQ measures valued living or the degree to which an individual accesses their chosen values in everyday life [59]. The VLQ is comprised of two 10-item scales, where participants rate the importance of different domains of life - family, intimate relationships, parenting, friendship, work, education, recreation, spirituality, citizenship and physical self-care - and subsequently rate the consistency with which they have acted in accordance with their values in the past week [59]. Wilson *et al*. [59] found the VLQ to demonstrate adequate-to-good internal consistency across domains.

For the secondary aim of the trial, relating to the mechanisms for change, process outcome measures have been developed for adolescents only and have been selected in accordance with the domains hypothesized to be associated with treatment efficacy in line with results of previous research (described above). As such, primary process outcome measures include experiential avoidance, cognitive fusion, acceptance and valued living (Table 2).

**Table 2 T2:** Primary outcome measures as they relate to the mechanism of change aim

**Mechanisms of change outcome measures**	**Assessment tool/measured factor**
Experiential avoidance	AFQ-Y, PANAS-X, TAS-20
Cognitive fusion	AFQ-Y
Acceptance	CAMM-20
Valued living	VLQ

AFQ-Y, Avoidance and Fusion Questionnaire - Youth; CAMM-20, Child and Adolescent Mindfulness Measure; PANAS-X, Positive and Negative Affect Schedule; TAS-20, Toronto Alexithymia Scale; VLQ, Valued Living Questionnaire.

#### Intervention

Participants allocated to ACT or CBT groups will complete a group-based therapy program of 10 × 1.5 hour sessions of the applicable treatment at CHW, which will be provided at no cost. Up to eight children or adolescents will be involved in each group program. Treatment will be conducted by between two and four psychologists, dependent upon final group numbers. All psychologists involved in the delivery of the intervention have been equally trained in both ACT and CBT, with the exception of one who has advanced training in CBT and intermediate training in ACT.

Caregivers will be involved concurrently in a “parent-as-coach” manner. Across both programs, the treatment will incorporate aspects that involve the participants and caregivers working independently of one another, as well as aspects that require working together. Both programs will also require regular completion of between-session practice tasks by both caregiver and the participant that will be reviewed at the subsequent session.

Both ACT [60-62] and CBT [63-65] programs will be based upon treatment manuals, tailored to the needs of participants. Manuals have been developed for children, adolescents, caregivers and therapists. Each program incorporates a series of psychological techniques consistent with the therapeutic modality employed. However, there are some commonalities across both interventions including psychoeducation, skills training and exposure. Although exposure to feared situations is a prominent technique employed across both ACT and CBT, the approach differs across therapies. In CBT, the focus is on challenging maladaptive thinking to enable performance of the exposure behavior, whereas in ACT, children or adolescents are encouraged to attempt to alter the relationship they have with their anxiety by distancing themselves from it and increasing their willingness to experience it.

### CBT program - Cool Kids (ages 7 to 11 years) and Chilled® (ages 12 to 17 years)

The CBT program will comprise the Cool Kids and Chilled® Programs developed at the Centre for Emotional Health, Macquarie University [66]. The effectiveness of Cool Kids and Chilled® in treating anxiety has been empirically demonstrated [66]. Cool Kids and Chilled® assist children and adolescents, respectively, to learn skills to recognize their emotions and combat anxiety, encouraging brave behavior and gradual engagement with feared situations. Because CBT is currently the most empirically supported therapeutic approach for children and adolescents [8], it was determined to be the most stringent comparison condition to employ within this trial. The ‘worry wave’ section of the Cool Kids and Chilled® Programs will be omitted for the purposes of this research as it was considered to have mindfulness components more consistent with an ACT approach. This is a small component of the overall program.

### ACT program - Cool Mind (ages 7 to 11 years) and Mindchill (ages 12 to 17 years)

The Cool Mind for Kids and Mindchill programs have been developed at CHW. They are both adaptations of the Cool Kids and Chilled® programs and were designed to conform to the overarching structure of these programs for comparison purposes. Cool Mind for Kids and Mindchill were developed on the basis of ACT-consistent protocols adapted from the Mindfulness-Based Cognitive Therapy for Children protocol [2]; Acceptance and Commitment Therapy Adapted for Children protocol [67], MiCBT protocol [68], and ACT Mindfully Workshops [69]. These programs incorporate all six ACT core therapeutic processes that target psychopathology including Acceptance, Being Present/Mindfulness, Valued directions, Committed Action, Self-as-context and Cognitive defusion. Children will learn skills to manage the distress associated with anxious thoughts and feelings. For example, whereas CBT attempts to dispute and modify unrealistic thoughts, ACT supports children to identify their values and behave in a value-consistent way. At the same time acceptance of anxious thoughts and feelings that may arise in the process of doing so is encouraged, as is learning to defuse these thoughts and feelings. While the content is similar for Cool Mind for Kids and Mindchill programs, the language is simplified for the child program and there is a greater focus on values for the adolescent program. Table 3 provides a session-by-session outline of the programs.

**Table 3 T3:** Session-by-session overview of the Acceptance and Commitment Therapy programs, Cool Mind and Mindchill

**Session**	**Mindchill program (adolescents)**	**Cool Mind for Kids program (children)**
1	Introductions, group expectations and an emphasis on the importance of practice tasks; psychoeducation on anxiety, values and feelings; introduction to acceptance and mindfulness as alternatives to ‘getting rid’ of unpleasant thoughts and feelings. Practice tasks: Mindful smiling	Introductions, group rules, psychoeducation on anxiety, learning about feelings, Feeling/worry scale, pink elephant and Chinese finger trap exercises to introduce the futility of control and acceptance as an alternative; introduction to mindfulness. Practice tasks: What I think and feel, mindful smiling/breathing whilst waking up
2	Barriers to mindfulness practice, mindfulness of the breath, mindful eating, choosing to live a valued life regardless of fear, mindful movement, rewards, Practice tasks: Additional mindfulness practice	Mindfulness of the breath, mindful eating, thoughts/feelings and control; anxiety and my body, psychoeducation on acceptance; mindful movement. Practice tasks: Mindfulness of the breath, mindfulness while lying down, mindfulness in everyday activities, ‘Me and My Body’ physiological aspects of anxiety
3	Mindful breathing; ‘milk, milk, milk’ exercise as introduction to defusion; mindful thinking; acceptance versus tolerance of anxiety. Practice tasks: Defusion and mindfulness exercises	Mindful breathing; ‘milk, milk, milk’ exercise as an introduction to defusion; introduction to and practice of defusion strategies; mindful thinking; introduction to rewards. Practice tasks: Defusion exercise, mindfulness of the breath, mindfulness in everyday activities
4	Body scanning; creating a fears and worries list; mindful thinking practice; introduction to stepladders (exposure) and first attempt to create own exposure hierarchy. Practice tasks: Body scanning, mindful thinking and working on personal stepladder	Body scanning; mindful thinking practice; creating a fears and worries list; introduction to stepladders (exposure) and first attempt to create own exposure hierarchy. Practice tasks: Daily body scanning, mindful thinking worksheets, create first stepladder
5	Imaginal exposure using stepladders; experiential avoidance and taking our worries with us through life; mindful thinking additional practice; revising stepladders. Practice tasks: Mindfulness practice and stepladders	Imaginal exposure using stepladders; experiential avoidance and taking our worries with us through life; mindful thinking for big worries; stepladders for big worries. Practice tasks: Body scanning, mindful thinking and exposure
6	Mindfulness practice, leaves on a stream exercise; judging versus describing, ‘unhooking’ from thoughts; letting go of negative self-judgements, acceptance. Practice tasks: Stepladders	Mindfulness practice, leaves on a stream exercise; judging versus describing, acceptance; working on stepladders for big worries. Practice tasks: Mindfulness meditation, imaginal exposure practice about the worst that can happen if he or she confronts the difficult situation and work on stepladders
7	Body scanning additional practice; dealing with set-backs or getting stuck; coping strategies; problem-solving skills building. Practice tasks: Body scanning and imaginal exposure on stepladders	Body scanning additional practice; mindful touch; problem-solving skills building; mindful thinking. Practice tasks: Mindfulness body scanning, exposure (both imaginary and real life)
8	Mindfulness practice; assertive communication; in-session exposure related to stepladders or fears and worries list; problem-solving any set-backs. Practice tasks: Mindful thinking worksheets with stepladders, seeking feedback for areas of self-doubt	Mindfulness practice; assertive communication; in-session exposure related to stepladders or fears and worries list; problem-solving any set-backs. Practice tasks: Mindfulness thinking, exposure in real life, practicing problem-solving
9	Mindful breathing additional practice; coping with teasing and bullying; external strategies to manage worries; review of progress towards goals; additional in-session exposure. Practice tasks: Act on one goal not yet achieved, family discussion of managing anxiety and stress in everyday life	Mindful breathing additional practice; outsmarting bullies; review of progress towards goals; additional in-session exposure. Practice tasks: Practicing describing thoughts rather than judging, practicing assertiveness, mindfulness activities, 10 minutes/day
10	Loving kindness meditation; reviewing goals; planning for the future; dealing with set-backs and celebrating success	Friendly wishes meditation; reviewing goals; focus on values guiding action; planning for the future; dealing with set-backs and celebrating success

### Controls

The control group in the study will be a waitlist group, also diagnosed with an anxiety disorder. Participants allocated to this group will complete baseline assessments and will receive CBT following a waiting list period of 10 weeks. This period was selected as it corresponds with the 10 week program, allowing for comparative post measure. It was considered unethical to withhold treatment for longer than 10 weeks.

### Treatment fidelity

Across the group treatment period, all psychologists will receive weekly group supervision. As the psychologists involved in the delivery of the treatment are involved in the delivery of both the ACT and CBT treatments, treatment fidelity is an important consideration that will be addressed via video-recording a subset of each 10 week program. Video-recording will be conducted with the consent of all participants and will be reviewed and analyzed by an independent assessor, for fidelity with the identified treatment (ACT or CBT) in accordance with a checklist designed for this study. The independent assessor will be a psychologist, with training in the use of both ACT and CBT, within the Department of Psychological Medicine who is not involved in the treatment groups. Two independent assessors will be employed to ensure reliability of treatment fidelity ratings. Feedback on the outcome of these reviews will be provided back to the research team and subsequently explored within weekly supervision. In line with the protocol of Forman *et al*. [70], therapist allegiance towards treatment will be assessed by having each psychologist respond to the question ‘Which treatment do you think leads to better outcomes, ACT or CBT?’. Therapist allegiance will be examined as a variable of interest in terms of any possible association with study outcomes.

### Sample size calculation

A power analysis was conducted to determine the approximate sample size required to achieve an examination of the effectiveness of a manualized ACT group-therapy program, the most sensitive aim. At a power level of 0.8, with an effect size (ES) of 0.6 to 0.7, it is estimated that a minimum 30 participants in each group is required to detect a significant difference between each of the three groups. The employment of analysis of covariance and mixed model statistical tests for pre versus post comparisons will also offer increased power to detect significant differences. The estimated ES of 0.6 to 0.7 is based on the results of three previous meta-analyses of ACT. In terms of primary outcome measures, Hayes *et al*. [31] observed that, compared to structured interventions, ACT was superior after treatment (*d* = 0.48) and at follow-up (*d* = 0.63). Ost [71] found that ACT was superior to established treatments achieving a mean ES of 0.68. In contrast, Powers *et al*. [72] found that, on primary outcome measures, ACT achieved ES in the range *g* = 0.42 to 0.68 when ACT was compared with control or waitlist conditions and *g* = 0.18 compared to established treatments. The ES for the current study is estimated in line with the higher-end ES results achieved across the aforementioned meta-analyses. The rationale for this is that these meta-analyses have incorporated studies for a range of low-prevalence disorders - disorders that are typically considered to be treatment resistant - whereas the current study focuses only on anxiety, high prevalent disorders, widely acknowledged to be more responsive to treatment.

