**Methods/design:**

We will recruit 150 young people (90 children and 60 adolescents) diagnosed with an anxiety disorder and their parent or caregiver. After completion of baseline assessment, participants will be randomized to one of three conditions (Acceptance and Commitment Therapy, Cognitive Behavior Therapy or waitlist control). Those in the Acceptance and Commitment Therapy and Cognitive Behavior Therapy groups will receive 10 × 1.5 hour weekly group-therapy sessions using a manualized treatment program, in accordance with the relevant therapy, to be delivered by psychologists. Controls will receive the Cognitive Behavior Therapy program after 10 weeks waitlisted. Repeated measures will be taken immediately post-therapy and at three months after therapy cessation.

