### Participants

Participants will be approximately 150 children (90 younger and 60 older children) aged 7 to 17 years with a primary diagnosis of a Diagnostic and Statistical Manual of Mental Disorders (DSM-IV) anxiety disorder. The participants will be age-classified as ‘children’, aged 7 to 11 years, and ‘adolescents’, aged 12 to 17 years. Twelve years of age was determined as the cut-off point to be consistent with other research involving ACT as a treatment for problems among adolescents [20].

Participants will be recruited via referrals to the Department of Psychological Medicine, The Children’s Hospital at Westmead (CHW), Sydney, NSW, Australia. Referrals will be accepted from anyone, including health professionals (general practitioners, psychologists, pediatricians), educational providers, and self-referrals. Written informed consent will be obtained from the parent or caregiver of the children and from the child/adolescent. Ethical approval was obtained for this study from the Human Research Ethics Committee at CHW and at The University of Newcastle.

The researchers predict that the majority of referrals will come from school counselors, followed by word of mouth, then via parents’ referral through the CHW intake phone line. In terms of proportions, it is expected that 60% to 70% of referrals will come from school counselors. On the basis of recruitment efforts to date and requests to intake phone line, the researchers consider that the anticipated sample will be achieved.

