### Statistical analysis

Data coding and analysis will be conducted using the IBM SPSS Statistics v.21 software program. Primary outcome measures will be examined both with intention-to-treat analyses and analyses conducted on treatment completers. For the efficacy hypotheses, paired t-tests and linear mixed models will be used to investigate changes in pre versus post primary and secondary outcome measures. Statistical significance will be considered as *P <*0.05. The mixed model approach has been selected as it allows for inter-participant and intra-participant variance as well as the inclusion of participants with missing data, whilst maintaining power.

In accordance with the protocol of Forman *et al*. [70], mechanism of change hypotheses will be examined using correlation and independent t-tests to determine which variables to include in a multivariate analysis of variance. Post-hoc multiple comparisons (for example, Bonferroni correction) will be performed to determine where significant differences lie. Multivariate regression examining factors related to treatment success will also be employed and will include examining any demographic (such as age, gender, family functioning) and clinical (such as pre-scores, psychological flexibility) factors that might be related to outcomes. Mediational analysis, a regression-based approach, will be used to test hypotheses about the mechanisms behind outcome, as this is a powerful way of determining mechanisms by which an effect operates rather than the existence of an effect [73]. It allows for more than one mediator and adjusts all paths for the potential influence of covariates not proposed to be mediators in the model. Receiver operating curve plots of the true positive and false positive rate for different possible cut-points of the regression test will be conducted because receiver operating curves convey information relating to the trade-off between sensitivity and specificity, and maximize predictive value. The coordinates of the receiver operating curve will be used to determine the optimal cut-point for the test. The full information maximum likelihood method will be used to deal with missing data.

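### Thirty per group does not give 0.8 power at ES 0.6 to 0.7: an unadjusted two-sided 5% pairwise test needs 34 to 45 per group, and the plan does not say whether its minimum applies pooled or per age group

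*Protocol article*

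**What the plan says.** The section headed Sample size calculation sets its inputs with "At a power level of 0.8, with an effect size (ES) of 0.6 to 0.7" and concludes that "it is estimated that a minimum 30 participants in each group is required to detect a significant difference between each of the three groups". It says the calculation was made "to achieve an examination of the effectiveness of a manualized ACT group-therapy program, the most sensitive aim". It then presents analysis of covariance (ANCOVA) and mixed models as a further source of power, and gives no baseline correlation.

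The significance level comes from the Statistical analysis section: "Statistical significance will be considered as *P <*0.05". Neither section says whether the test is one-sided or two-sided.

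On numbers, the Participants section states: "Participants will be approximately 150 children (90 younger and 60 older children) aged 7 to 17 years". The abstract gives the same 90 and 60 split and says that "participants will be randomized to one of three conditions". The allocation ratio is not given.

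**The concern.** The words "to detect a significant difference between each of the three groups" describe pairwise comparisons between arms. For a standardized difference of 0.6 to 0.7 at the usual two-sided 5% level, 30 per group looks too few for 80% power.

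Two things are at stake. First, a reader will take 30 per arm as an 80%-power design, and so may misjudge any comparison of about that size. Second, the article does not say what unit the minimum applies to. Ninety children over three arms is exactly 30 per arm, so a reader could take any child-only or adolescent-only comparison as adequately powered and over-interpret a null result there.

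**Working it through.** **Inputs.** Power 0.8 and ES d = 0.6 to 0.7, SD = 1 (Sample size calculation). Alpha 0.05 (Statistical analysis). Assumptions: two-sided test, equal allocation, no adjustment for covariates or multiplicity.

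**Step 1: try to reproduce 30.** The normal approximation is n per group = 2(z₀.₉₇₅ + z₀.₈)² / d² = 2(1.960 + 0.842)² / d² ≈ 15.70 / d².

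- d = 0.6: 15.70 / 0.36 = 43.6, so 44
- d = 0.65: 15.70 / 0.4225 = 37.2, so 38
- d = 0.7: 15.70 / 0.49 = 32.04, so 33

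The exact t-test (noncentral t, 2n − 2 degrees of freedom, noncentrality d√(n/2)) adds one per group: **45, 39 and 34**. Thirty is not reached anywhere in the stated range. Over three arms the need is 3 × 34 = 102 to 3 × 45 = 135.

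**Step 2: power at the sample sizes the plan implies.** The approximate formula is Φ(d√(n/2) − 1.960). For n = 30 and d = 0.6, this is Φ(0.6 × 3.873 − 1.960) = Φ(0.364) = 0.64; the t-test gives 0.63. The t-test values are:

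| n per arm | Source | Power, ES 0.6 | Power, ES 0.7 | ES detectable at 80% power |
|---|---|---|---|---|
| 30 | stated minimum; also 90 children / 3 | 0.63 | 0.76 | 0.74 |
| 20 | 60 adolescents / 3 | 0.46 | 0.58 | 0.91 |
| 50 | 150 pooled / 3 | 0.84 | 0.93 | 0.57 |

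**Step 3: variants that might have produced 30.**

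- *One-sided 5% t-test:* 36, 30 and 26 per group at ES 0.6, 0.65 and 0.7. It matches 30 at the midpoint, but power at n = 30 and ES 0.6 is 0.74.
- *Three-group omnibus test, one arm differing from two equal arms by d:* about 42 per group at ES 0.6 and 31 at ES 0.7. Power at n = 30 is 0.65 to 0.79. This test also does not address a difference between each pair of arms.
- *ANCOVA, two-sided:* adjustment scales the residual variance by 1 − r², where r is the baseline correlation. Reaching 80% at n = 30 requires d / √(1 − r²) = 0.736, so r = √(1 − (d / 0.736)²). This gives r of about 0.58 at ES 0.6 and 0.31 at ES 0.7.

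No unadjusted variant tried reaches 0.8 with 30 per group at the lower end of the range. ANCOVA does so only with a correlation that the plan does not state.

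**The case against.** The best defence is that the article is condensed, calls its sample size approximate, and leaves the test and sidedness unstated. Thirty could come from a one-sided test at the midpoint ES, or from an omnibus or covariate-adjusted calculation near the upper end. The planned between-group analysis is a mixed model rather than an unadjusted t-test. With an assumed baseline correlation of 0.5, ANCOVA power would be 0.75 to 0.87 at 30 per arm and 0.57 to 0.70 at 20 per arm.

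Part of this stands. It would be wrong to say that 30 can arise in only one way, and the t-test figures are not the power of the final model. But none of these routes supports 30 across the whole stated range without an undeclared input, and the section offers covariate adjustment as a bonus on top of the 30. Needing 34 to 45 instead of 30 is 13% to 50% more per group, which is more than rounding.

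Three stronger readings are tempting, and the document does not support them.

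- *A reader might infer that the trial is underpowered.* Recruitment is planned at 150. With equal allocation, 50 per arm exceeds both the stated 30 and the recomputed 45.
- *A reader might infer that adolescents, at 20 per arm, miss the plan's own minimum.* The minimum is worded for the three arms. The efficacy hypotheses in the Background name children and adolescents together, the 3 × 3 design has no age factor, and no age-specific efficacy test is stated. Only the mechanism aim is confined to adolescents, and the sample size section powers a different aim. That 90 = 3 × 30 is a hint, not a statement.
- *A reader might fault the lack of a drop-out allowance.* The full protocol may hold one, and on the pooled reading 150 leaves a margin over the requirement.

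**Conclusion.** The sample size statement is wrong as written on the ordinary reading. At two-sided 5%, 30 per group falls short of 0.8 power at every point of the stated ES range, and the requirement is 34 to 45 per group. This rests on two-sided testing and an unadjusted pairwise comparison. Under one-sided testing, the statement still fails at ES 0.6.

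The consequence depends on the unit, which the article leaves open. For a pooled efficacy comparison at the stated ES, planned enrolment is sufficient on paper, before drop-out and therapy-group clustering, and only the sentence is at fault. If the minimum was meant per age group, neither group reaches 0.8 unadjusted, and adolescents also fall below 30. In either case, an adolescent-only between-arm comparison at 20 per arm has roughly even odds of detecting the effect the plan assumes.

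**What to change.** In the Sample size calculation section:

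1. Replace the 30-per-group figure with 34 to 45 per group for ES 0.7 to 0.6, and state that it is for a two-sided 5% pairwise test without covariate or multiplicity adjustment. If another test or sidedness was used, state it, along with any baseline correlation relied on.
2. Give the power at planned enrolment: 84% to 93% per pairwise comparison at 50 per arm pooled, before drop-out and clustering.
3. State whether the minimum applies to the pooled arms or within each age group, and state the allocation ratio.
4. For any age-specific between-arm comparison, report its own unadjusted power (63% to 76% for children, 46% to 58% for adolescents), so that a null result is not read as coming from an 80%-power test.

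The cost is a few sentences and a less favourable stated figure. No change to recruitment is needed.
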